### Participants’ eligibility and recruitment

Participants will be recruited via flyers, newspaper advertisement, or newsletters. For an inclusion, they will need to be between 60–75 years of age, fluent in German, right-handers, non-smokers, with normal or corrected-to-normal vision, and no history of severe psychiatric or neurological disorders. In addition, their Montreal Cognitive Assessment score (MoCA) [25] will need to be ≥ 23 and their Geriatric Depression Score (GDS) [26] will need to be ≤ 6. To ensure comparable verbal intelligence, all participants will complete a German vocabulary test (Wortschatztest, WST) [27]. Exclusion criteria will be severe colour blindness, past head injuries, dermatosis, metal implants in the head-area, current or lifetime seizures, alcohol or drug abuse, intake of medication that interferes with cognition, as well as brain damage.

All participants will give written informed consent prior to testing. The Cantonal Ethics Committee Bern approved the study, which will be conducted according to the Declaration of Helsinki.

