### Randomization

A total of 105 healthy older adults will be included, stratified by age and sex. All participants will be randomly assigned to one of six experimental groups or the control condition (i.e., sham stimulation). They will receive anodal or cathodal high-definition tDCS of the right inferior frontal lobe, the left inferior frontal lobe, or the right superior parietal lobe, or sham. For sham stimulation, we will randomly place the electrodes over the same regions. Randomization will be done by JP based on a Matlab script written by TR (allocation ratio 1:5, stratified by age and sex). Neither JP nor TR will be involved in data collection. The study will follow a double-blind design, such that neither the participants nor the experimenter will be aware of the stimulation condition. Unblinding will occur at the end of data acquisition. Exceptions will only be allowed in case of adverse events.

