**Fig 2 pone.0289532.g002:**
[figure not shown]
Study procedure. There will be two assessments with similar setups. Only during the second assessment, participants will receive high definition-transcranial direct current stimulation (HD-tDCS) for 20 minutes with 1 milliamp.

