### Statistical analysis

Our primary outcome measures will be performance in attentional control and laboratory prospective memory tasks: From the ANT, we will evaluate the controlling variable. From the TAP, we will use the number of false alarms in the Go/No-Go tasks, correct answers in the flexibility task, the number of missed targets in the dual task, and mean reaction times. For laboratory prospective memory, accuracy and reaction times will be evaluated. We will use mixed ANOVAs or mixed effects models for statistical analysis of stimulation effects on primary outcome variables (depending on whether there will be any missing data). In contrast to an ANOVA, mixed effects models are better capable of handling missing data and they also allow an analysis of data on a trial level while taking hierarchical structures of data and variability within subjects into account. We will use session (first, second) as within-subject factor and condition (six experimental groups or sham) as between-subject factor. We will determine whether inhibiting or enhancing activity in the left or right frontal inferior lobe or the right superior parietal lobe will modulate attentional control or prospective memory.

As secondary outcomes, we will evaluate accuracy of the ongoing task as well as ICV of reaction times during attentional control or the ongoing-task of the laboratory prospective memory paradigm. In addition, we will test whether stimulation will have any effect on alerting or orienting (i.e., ANT Task). We will then test whether attentional control significantly predicts laboratory, naturalistic, or self-reported prospective memory using multiple linear regression.

Further we plan to model laboratory prospective memory responses by using multinomial modelling of response probabilities [51]. This approach estimates both the prospective component (i.e., remembering *that* you have to do something) and the retrospective component (e.g., remembering *when* and *what* you have to do) of prospective memory.

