We will include age as a covariate in all models since it significantly influenced prospective memory in our previous study [52]. We will control for any potential influence of mood or agitation on cognition and test, in an exploratory analysis, whether mood or heart rate of participants will influence attentional control or prospective memory. Further we examine, whether one of these two measures are modulated by non-invasive brain stimulation. For an assessment of heart rate, we will include changes in beats per minute (relative to baseline) between the start of stimulation until two minutes after its end (i.e., 22 minutes). Generalized estimated equations will then be used to test any longitudinal stimulation effects on heart rate during the stimulation session [53–55].

We will use R (version 4.2.1) with RStudio (version 2022.02.3) for statistical analyses with *p* < 0.05 considered statistically significant. We will correct for multiple-comparisons using Bonferroni-Holm correction. Whenever the assumptions of normality and homogeneity are not met, data will be transformed and/or non-parametric alternatives will be used. We will only analyse data of participants that attended both sessions.

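### The plan does not say whether age interacts with session; as a main effect only, age cannot adjust the session × condition test on session-level data, and the ANOVA and mixed-model routes may differ

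*Protocol article*

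**What the plan says.** All references are to the protocol article.

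- **Age term** (Statistical analysis): "We will include age as a covariate in all models since it significantly influenced prospective memory in our previous study". No model formula is printed, and an age × session term is neither named nor excluded.
- **Factors** (Statistical analysis): "We will use session (first, second) as within-subject factor and condition (six experimental groups or sham) as between-subject factor".
- **Model class** (Statistical analysis): "We will use mixed ANOVAs or mixed effects models for statistical analysis of stimulation effects on primary outcome variables", the choice depending on missing data. Of mixed models it adds that "they also allow an analysis of data on a trial level while taking hierarchical structures of data and variability within subjects into account".
- **Analysis set** (Statistical analysis): "We will only analyse data of participants that attended both sessions".
- **Timing of stimulation** (Fig 2 legend): "Only during the second assessment, participants will receive high definition-transcranial direct current stimulation (HD-tDCS) for 20 minutes with 1 milliamp".
- **Age in the design**: "A total of 105 healthy older adults will be included, stratified by age and sex" (Randomization). For eligibility, "they will need to be between 60–75 years of age" (Participants' eligibility and recruitment).

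**The concern.** The article does not name the term that carries the stimulation effect, but the design leaves little choice. The first session is unstimulated for everyone and the second is stimulated or sham, so the effect is the difference between conditions in the change from session 1 to session 2, that is, session × condition.

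A participant's age is the same in both sessions. A main effect of age moves both values by the same amount and disappears from the change. The adjustment would then do no work in the test of most interest, and any relation of age to practice gain would stay in the error term.

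The word covariate also does not mean the same thing in every routine. Some repeated-measures ANOVA functions cross a between-participant covariate with the within-participant factor automatically. A mixed model does so only if the analyst writes the term. One sentence of the plan can therefore yield two different tests of the same primary outcome.

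**Working it through.** **Inputs from the article.** Seven conditions of 15 participants (N = 105), two sessions, significance level 0.05, age 60–75. The plan gives no figure for the effect of age on performance or on change, so there is nothing of its own to reproduce here. Every age slope and variance share below is an assumption.

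**Step 1: algebra.** For participant *i* in condition *g*, with an age main effect and a participant intercept *u*:

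- session 1: y₁ = μ₁ + α_g + β·age + u + e₁
- session 2: y₂ = μ₂ + α_g + γ_g + β·age + u + e₂
- change: y₂ − y₁ = (μ₂ − μ₁) + γ_g + (e₂ − e₁)

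β is gone. The γ_g, which are the stimulation effects, are estimated from the change alone. Adding age × session with slope δ leaves δ·age in the change, which amounts to analysing the change score adjusted for age.

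**Step 2: check on simulated data** (7 × 15 participants, one value per session, one dataset per row). The entries are F for session × condition.

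| Routine | Assumed age slope on change | No age | Age main effect | Age × session |
|---|---|---|---|---|
| Random-intercept model | 0 | 1.985 | 1.985 | 1.962 |
| Random-intercept model | 0.1 SD per year | 0.957 | 0.957 | 0.616 |
| R, other dataset | 0 | 3.158 | 3.158 (aov) | 3.125 (car::Anova) |
| R, other dataset | 0.1 SD per year | 1.241 | 1.241 (aov) | 1.636 (car::Anova) |

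The main effect leaves F unchanged even when age truly predicts change. In the R rows both routines were given age simply as a covariate. aov with an error stratum kept it as a main effect (6 and 98 df for the test), while car::Anova added age × session by itself. Single datasets show that the tests differ; F can move either way, so they do not measure a gain.

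**Step 3: where the cancellation is only approximate.**

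- Trial-level model with unequal trial counts: F 2.018 without age and 2.015 with it; one coefficient moved from 0.742 to 0.755.
- Some session values missing: F 1.465 without age and 1.471 with it.
- Binomial model of 12 cues: Wald statistic 4.770 without age and 4.798 with it (with convergence warnings).

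The age main effect is nearly inert in these cases, but not exactly so.

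**Step 4: possible gain in precision.** If age explains a share R² of the variance of change, the error variance shrinks by the factor 1 − R² and the noncentrality becomes λ = N·f²/(1 − R²), with 6 and 97 df. The starting value f² = 0.138 is chosen because it gives 80% power at N = 105.

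| Assumed R² | λ = 105 × 0.138/(1 − R²) | Power |
|---|---|---|
| 0 | 14.49 | 80% |
| 4% | 15.09 | 82% |
| 9% | 15.92 | 84% |
| 16% | 17.25 | 87% |

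**The case against.** **The plain age term is not in the text.** The article says only that age is a covariate and excludes nothing. An exact formula is something an article commonly leaves to the full plan. This stands. A reader might infer that the planned adjustment does nothing, or that the reported adjusted effect will equal the unadjusted one. The article does not support that as a fact; it holds only if age enters without session. What remains is that two routes are explicitly allowed and the same wording can mean different tests in them.

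**Attending both sessions is not the same as having complete outcomes.** The choice of model is tied to missing data, and trial-level analysis is mentioned. This also stands: exact cancellation is confined to one value per participant and session with both present. The shifts found elsewhere were small.

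**Age is not idle in the plan.** It adjusts between-participant comparisons and the regressions of prospective memory on attentional control. The reason given for it concerns level of performance, which a main effect matches. Correct.

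**Nothing is biased.** Condition is randomised with stratification by age, so omitting age × session does not distort the stimulation effect. Correct; a reading of this point as a bias would be wrong.

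**The gain may be nil.** If age is unrelated to change, F barely moves (1.985 to 1.962; 3.158 to 3.125). The 80% starting power is assumed. The article's own η² = 0.32, read as the effect on this test, gives f² = 0.32/0.68 = 0.47 and power above 99% at N = 105, leaving almost nothing to gain. This limits the size of the point, though not the ambiguity.

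**Conclusion.** The point holds in a conditional form. If age enters as a main effect only, it cannot adjust the session × condition test on session-level data from participants with both sessions, and it does almost nothing in trial-level models. Because some R routines add age × session and others do not, the ANOVA and mixed-model routes could test different things on identical data.

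The consequence is an avoidable analyst choice across several primary outcomes and perhaps some lost precision. The test remains valid either way. On assumed values (80% starting power; age explaining 4–16% of the variance of change) the gain would be 2 to 7 percentage points of power. It is zero or slightly negative if age does not predict change. This is an optional improvement, not a correction of an error.

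**What to change.** In Statistical analysis, extend the sentence on age to say that centred age and its interaction with session are included in all session × condition stimulation models, in the mixed-ANOVA and mixed-model routes alike. The regressions can keep age as an ordinary covariate.

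The cost is one line of specification and one degree of freedom (error df 97 instead of 98 for session-level data). No new data are needed, since age is already recorded and used for stratification.

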### Study procedure

All participants will be tested twice to differentiate learning effects from stimulation effects (Fig 2). All assessments will be done by the same examiners (NS, RM) at the University Hospital of Old Age Psychiatry and Psychotherapy at the University of Bern, Switzerland. On the first day of the experiment, we will test verbal intelligence [27], followed by an assessment of current mood (Profile of Mood States, POMS; Positive and Negative Affect Scale, PANAS) [28–30]. Then, the participants will put on a wearable device (Polar Verity Sense by Polar Electro Europe AG, polar.ch) on their left arm that will monitor their heart rate. Next, they will be asked about how many hours they had slept the night before and how awake and motivated they currently feel. Then, the attention network task and the prospective memory task will follow. Next, they will do a Go/No-Go task, a flexibility task, and a divided attention task (TAP) [31]. Finally, they will again rate their current mood and different naturalistic prospective memory tasks will follow. The second day of the experiment will be identical with the exceptions that we will apply stimulation for 20 min during the attention network task and the prospective memory task and that there will be no verbal intelligence test. At the end of the experiment, side effects, and the participants’ perception of the stimulation condition will be captured [32].

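### Limiting every analysis to participants who attended both sessions discards usable session-1 data and removes the missed sessions that a mixed model could handle

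*Protocol article*

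**What the plan says.** Three statements in the Statistical analysis section of the protocol article bear on this.

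- The model is to be a mixed ANOVA or a mixed-effects model, "depending on whether there will be any missing data". The reasons given are that "mixed effects models are better capable of handling missing data and they also allow an analysis of data on a trial level".
- The design is set out as follows: "We will use session (first, second) as within-subject factor and condition (six experimental groups or sham) as between-subject factor".
- The section closes with the analysis set: "We will only analyse data of participants that attended both sessions". No analysis is exempted, and neither an all-randomised analysis nor a sensitivity analysis is described.

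Study procedure places stimulation on the second day only: "The second day of the experiment will be identical with the exceptions that we will apply stimulation for 20 min". Session 1 is therefore unstimulated for everyone. The same Statistical analysis section plans multiple linear regressions of laboratory, naturalistic and self-reported prospective memory on attentional control. It does not say which session supplies the data.

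**The concern.** With two sessions and a between-subject condition, a missed session is the main kind of missing data that a mixed model can use and a mixed ANOVA cannot. The closing rule deletes exactly those participants first. The section thus gives missing-data handling as a ground for the model and then withholds from the model most of the missing data it could handle.

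Two things are at stake. In the stimulation analysis, session-1 measurements from randomised participants who do not return are not used. In the regressions, a participant with session-1 attentional control and a session-1 prospective memory outcome is dropped for missing a visit that those particular analyses may not need.

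**Working it through.** **Inputs from the article.** Two sessions by seven conditions; 15 per group, 105 in total (Sample size calculation); stimulation in session 2 only (Study procedure). No drop-out rate is given, so there is no figure of the plan's own to reproduce on this point.

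**Assumptions.** A share d of participants misses session 2, with d = 5–15% and equal across groups. The between-session correlation is r = 0.3–0.7. The variance is 1 in both sessions, and missingness is at random.

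**1. Session-by-condition contrast.** Let n be the number per group and n_c = n(1 − d) the number who return. The variance of the estimated mean change in one group is:

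- both-session attenders only: [(1 − r²) + (1 − r)²] / n_c
- with session-1-only participants kept: (1 − r²) / n_c + (1 − r)² / n

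The ratio of the second to the first is [(1 + r) + (1 − r)(1 − d)] / 2 = 1 − d(1 − r)/2.

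- Smallest gain (d = 0.05, r = 0.7): 0.05 × 0.3 / 2 = 0.0075. Variance falls by 0.75%; the standard error is multiplied by √0.9925 = 0.996, about 0.4% lower.
- Largest gain (d = 0.15, r = 0.3): 0.15 × 0.7 / 2 = 0.0525. Variance falls by 5.25%; the standard error is multiplied by √0.9475 = 0.973, about 2.7% lower.

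**2. Worked example.** With 15 per group, 2 per group missing session 2, and two groups compared on change, the standard errors in SD units are:

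| r | 13 attenders only | 2 session-1-only kept | No loss (15) |
|---|---|---|---|
| 0.3 | 0.464 | 0.453 | 0.432 |
| 0.5 | 0.392 | 0.386 | 0.365 |
| 0.7 | 0.304 | 0.301 | 0.283 |

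The gain is about 1–2%. At r = 0.5, keeping the session-1 data recovers 0.3922 − 0.3856 = 0.0066 of the 0.3922 − 0.3651 = 0.0271 lost, roughly a quarter. The rest cannot be recovered, because the stimulated outcome was never observed.

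**3. Regression on session-1 data.** The standard error scales as 1/√n, so the rule inflates it by 1/√(1 − d) − 1. This is 2.6% at d = 0.05 and 8.5% at d = 0.15.

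**4. Which regression outcomes a session-1-only participant has.**

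| Outcome | When given | Available after session 1 alone? |
|---|---|---|
| Laboratory prospective memory | both sessions | yes |
| Naturalistic tasks | both sessions, one version each | yes, if scored per session |
| PRMQ | session 1 | yes |
| MPMI-s | session 2 | no |

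**5. Bias.** If returning depends only on the predictors, a correctly specified regression slope remains unbiased, and the loss is one of range and precision. Bias requires that returning depends on the outcome given the predictors. That could happen here, since keeping an appointment is itself a future intention, but the article has no return data with which to judge it.

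**The case against.** The best case for the rule is that it costs little and leaves the mixed model with a job to do. Much of that stands.

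- A reader might infer that the rule cancels the reason for using mixed models. The article does not support this. Trial-level analysis is a separate stated reason and is untouched. Attending both sessions also does not guarantee complete data: the HD-tDCS section allows stimulation to be aborted, and single tasks or reaction times can be missing.
- A reader might infer that the stimulation comparison is biased by drop-out. Stimulation is given only in session 2, and "neither the participants nor the experimenter will be aware of the stimulation condition". Someone who never attends that session cannot have stayed away because of the stimulation received. The article also does not say whether randomisation precedes session 1, so the number of randomised participants dropped is unknown.
- A reader might infer that session-1-only participants have complete data for the whole regression aim. They do not: they lack the MPMI-s. The naturalistic outcome is a sum that the text allows to span both sessions, in which case it would be incomplete too.
- The regression figure applies only if session-1 data are used, a choice the article leaves open.

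The objection does not remove the mismatch between the two statements, nor does it give a reason for discarding session-1 data where they are usable.

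**Conclusion.** The point holds as a modest one. The both-sessions rule is stated without qualification, and it removes the missed sessions that the same section's missing-data argument would naturally cover. At an assumed 5–15% loss and a between-session correlation of 0.3–0.7, the avoidable loss is about 0.4–2.7% in the standard error of the session-by-condition contrast. In any regression built on session-1 data it is 2.6–8.5%. These figures rest on assumed rates, not on anything the article reports.

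This is mainly a loss of precision. It would go too far to call the stimulation effect biased by the rule, or to say that the regression is biased. The latter would need return to depend on the outcome given the predictors, which the article neither shows nor excludes. The change is worth making because it reconciles the section with itself and costs almost nothing.

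**What to change.** Replace the closing rule of the Statistical analysis section with three statements, settled before unblinding:

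1. The mixed-effects model includes every randomised participant with data from at least one session.
2. Each regression includes every participant who has the predictor and that outcome. Examples are session-1 attentional control with session-1 laboratory prospective memory, with the session-1 naturalistic score, or with the PRMQ. The MPMI-s regression remains limited to those who attended session 2.
3. The both-sessions set is kept as a sensitivity analysis.

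Two clarifications are needed for this to work: which session feeds each regression, and whether the naturalistic sum is formed per session. The authors should also report how many participants missed session 2, by group, and say whether randomisation came before session 1. The cost is a few sentences and one additional model run, with no new data.

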### Sample size calculation

We used G*power [56] for the determination of sample size. Calculations were based on a previous non-invasive brain stimulation study in healthy young participants [22]. The effect size in this study (*η*² = 0.32) suggested a required sample size of n = 93 to detect robust effects in an ANOVA design with seven groups. We have increased the sample size to n = 15 in each group and will, therefore, include n = 105 healthy older individuals.

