## Introduction

The ability to perform an intended action at a future point in time is referred to as prospective memory. How well we remember these intentions seems to depend on attentional control, which enables us to direct (or shift) attention and to inhibit responding to distractions [1, 2]. Attentional control predicts laboratory prospective memory across all ages [3–6]. At a neuronal level, there may be a link between attentional control and prospective memory as well since, for example, the inferior frontal gyrus as well as the superior parietal lobe were active during both tasks in younger and middle-aged adults (see [7] for a meta-analysis). There is an ongoing debate, however, whether increased or decreased activity in these brain regions is beneficial for older adults’ attentional control [8–12] or prospective memory [13–16]. In the context of ageing, understanding the differential role these areas have for both cognitive functions would be important. To this end, modulating activity in these areas during these tasks can provide dynamic insights. This may help to develop further current models of how they are involved in attentional control and prospective memory in healthy ageing and to predict what goes wrong in diseases. So far, activity in the left or right inferior frontal gyrus or the superior parietal lobe was modulated during attentional control tasks. It was found that activity in the right hemisphere was particularly relevant for attentional control in both younger and older adults [17–21] although excitatory protocols (e.g., anodal stimulation) did not necessarily led to performance gains. For prospective memory, increasing activity in the left superior parietal lobe improved younger adults’ prospective memory more than increasing activity in the right superior parietal lobe [22, 23]. It is not completely understood, however, whether this effect generalizes to older adults, and/or whether modulating other brain regions such as the left or right inferior frontal gyrus has similar effects on prospective memory.

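### The stated requirement of n = 93 cannot be reproduced from the cited eta-squared of 0.32, and the paragraph does not show what 15 per group can detect against sham

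*Protocol article*

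**What the plan says.** The Sample size calculation section of the protocol article names G*Power as the tool and gives the origin of the planning effect: "Calculations were based on a previous non-invasive brain stimulation study in healthy young participants". It then links effect and result directly, saying that the eta-squared of 0.32 "suggested a required sample size of n = 93 to detect robust effects in an ANOVA design with seven groups". The design is described only as an ANOVA with seven groups. The group size is then rounded up to 15, which gives 105.

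The Statistical analysis section sets the significance level ("with *p* < 0.05 considered statistically significant"), a Bonferroni-Holm correction whose family is not named, and the model: "We will use session (first, second) as within-subject factor and condition (six experimental groups or sham) as between-subject factor". Only participants who attended both sessions are analysed. The Randomization section describes six active groups and one sham group.

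The article gives no target power, test family, or correlation between sessions for the sample size.

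**The concern.** A sample size statement should let a reader go from the stated effect to the stated number. Here an effect as large as eta-squared 0.32 should need far fewer than 93 people, so either the effect that was entered is not the one cited, or settings were used that the text does not report.

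At stake is what the reader believes the trial can show. The paragraph suggests that 105 comfortably exceeds the need. But the hypotheses in the Introduction differ by region, and the aim is to learn whether stimulating or inhibiting each region changes performance. Those questions come down to contrasts of 15 active against 15 sham participants, and the paragraph says nothing about the precision of such contrasts.

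**Working it through.** **Inputs from the article.** Eta-squared 0.32; seven groups; stated requirement 93; 15 per group, total 105 (Sample size calculation). Alpha 0.05 (Statistical analysis). **Assumed, because not stated.** Power 80% to 99%; session correlation rho 0 to 0.8; six active-versus-sham contrasts as the Holm family.

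**Step 1: try to reproduce 93.**

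f = sqrt(eta² / (1 − eta²)) = sqrt(0.32 / 0.68) = 0.686, so f² = 0.4706.

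One-way ANOVA: noncentral F with df1 = 7 − 1 = 6, df2 = N − 7, noncentrality = f² × N. The smallest N that reaches each power is:

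| Power | N | Noncentrality |
|---|---|---|
| 80% | 36 | 16.9 |
| 90% | 44 | 20.7 |
| 95% | 52 | 24.5 |
| 99% | 67 | 31.5 |

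In equal groups these become 42, 49, 56 and 70. At N = 93 the noncentrality is 0.4706 × 93 = 43.8 and the power is 99.96%. So 93 is not reproduced.

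**Step 2: other standard settings.** Adding a covariate leaves the one-way figures unchanged. With two sessions, rho 0 to 0.8 and power 80% to 99%, the between-groups test needs 22 to 61 and the session-by-condition interaction 12 to 37. The most conservative effect-size option gives 42 to 73. None gives 93.

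**Step 3: what 93 would match.** Solving for f at N = 93, alpha 0.05 and 80% power gives f = 0.397, and eta² = 0.397² / (1 + 0.397²) = 0.136. A round f of 0.40 gives 92 with seven groups and 93 with 14 cells. Reading 0.32 as f instead of eta-squared gives 140 in a one-way test, but 93 in a repeated-measures between-groups test at rho = 0.3 and 80% power. More than one unreported setting can thus reach 93, so these are inferences, not a diagnosis.

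**Step 4: what N = 105 delivers for the omnibus test.** One-way, 80% power: f = 0.37, eta² = 0.12.

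**Step 5: one active group against sham.** Two-sided t test, 15 against 15, pooled error df = 105 − 7 = 98, noncentrality = d / sqrt(2/15). At 80% power, d = 1.03 at alpha 0.05, and d = 1.29 at 0.05/6 = 0.0083, the first Holm step for six contrasts. These are in SD units of the quantity analysed. Power at d = 0.5 is 27% unadjusted and 10% at 0.0083; at d = 0.8 it is 58% and 31%.

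For an analysis of change, the SD of the change is sqrt(2(1 − rho)) times the single-session SD, so the detectable difference in raw single-session SDs is:

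| rho | sqrt(2(1 − rho)) | Unadjusted | First Holm step |
|---|---|---|---|
| 0 | 1.414 | 1.46 | 1.83 |
| 0.5 | 1.000 | 1.03 | 1.29 |
| 0.7 | 0.775 | 0.80 | 1.00 |
| 0.8 | 0.632 | 0.65 | 0.82 |

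**The case against.** The strongest defence is that the error is on the safe side. The cited effect needs fewer than 93, and 105 exceeds 93, so on its own premise the trial is not too small. That stands, and it limits the severity. A related defence is that an article may leave power and software options to the full protocol. That also stands, so their absence is not the point here. The point is that the one effect and the one number that are printed do not belong together at any ordinary power.

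Several stronger readings are tempting, and the documents do not support them:

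- *The omnibus test was sized and the session-by-condition effect was not.* The text says only "to detect robust effects in an ANOVA design with seven groups". The planned mixed ANOVA also has seven conditions, so its interaction may have been what was sized.
- *An f of 0.40 was really used.* That match needs 80% power, which is not stated, and other settings reach 93 too.
- *Only differences of about 1 SD can be detected.* That is one scenario. The figure depends on the session correlation, and the plan also allows trial-level mixed models and adjusts for age, which may change the precision.
- *The planning effect comes from a brain region that is not stimulated here.* The Introduction, citing two studies together, says that "increasing activity in the left superior parietal lobe improved younger" adults' prospective memory more than the same on the right did. The right parietal lobe is an arm of this trial, and the article does not say which contrast gave 0.32. The difference in age is openly disclosed.
- *Null results for single arms will be read as no effect.* No section says so.

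**Conclusion.** The point holds as a fault of reproducibility and of incomplete information, and should be fixed. Eta-squared 0.32 calls for 36 to 67 participants in a seven-group one-way ANOVA at alpha 0.05 and 80% to 99% power, not 93. The cause cannot be settled from the article. The mismatch is conservative for the omnibus effect and gives no reason to change the sample size.

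What remains is that the paragraph does not show the sensitivity of the contrasts with sham. That sensitivity is modest: about 1.03 SD of the analysed quantity unadjusted, and 1.29 SD at the strictest Holm step. The second figure rests on an assumed family of six. Expressed in raw SDs, both rest on a session correlation that the article does not give; only a high one (0.7 to 0.8) brings the unadjusted figure down to 0.80 to 0.65. Several primary outcomes in one Holm family, or the loss of participants who miss a session, would raise these figures.

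**What to change.** Keep N = 105 and rewrite the Sample size calculation paragraph:

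1. Correct or remove the statement that eta-squared 0.32 requires 93.
2. Report the effect size, alpha, power and test actually entered in G*Power, including the session correlation if a repeated-measures test was used.
3. State that 105 participants give 80% power for an omnibus f of 0.37 (eta-squared about 0.12) in a one-way ANOVA.
4. Give the detectable difference between one active group and sham as a range over session correlation, with and without the Holm adjustment, and name the family assumed.
5. State that the single-arm contrasts with sham will be reported with confidence intervals.

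The cost is wording and the retrieval of the original G*Power settings. No participants, allocation or planned model change, which matters because recruitment began in May 2021 and data collection was still under way when the article was written. The stated justification will look less generous than it does now.
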